***Short version of the patient-directed intervention (historical control group)***

Patients in the historical control group receive a shortened version of the patient-directed intervention. The short version includes the information-giving section on the functioning of the spleen and on health implications of asplenia (targeting risk perception, outcome expectancy and task self-efficacy) as well as the motivational-section on the efficacy of the recommended precautions and on strategies for risk situations (targeting positive outcome expectancy and task self-efficacy) since it is important for ethical reasons that the control group is provided with the same precautionary information as the intervention group. However, the time-consuming planning-section is absent from the control group’s intervention as specific action plans and potential barriers are not discussed due to a lack of time resources. The intervention in the control group is implemented only for ethical reasons and is not an intervention variant to be evaluated. Data collection relevant for the study has already been completed in this group at the time of intervention implementation, thus a confounding influence on the outcome variables can be ruled out.

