**Participants and recruitment**

Participants are patients with anatomic asplenia and their physicians (general practitioner or specialists). Eligible are German-speaking patients aged 18 years or older, who are insured by the cooperating health insurance AOK Baden-Württemberg, which is Germany’s 5^th^ largest health insurance and insures more than four million people.

Patient participants are preselected to either the intervention or control group based on the time interval since they underwent splenectomy. Patients who are recently splenectomized (at most 4 months) are allocated to the intervention group. Potential intervention patients are recruited about 6-8 weeks after splenectomy successively by biweekly request from February 2019 for a maximum period of 18 months. The historical control group consists of patients who are splenectomized since more than six months (at most 18 months). Thus, pre-interventional baseline-data on primary and secondary outcomes in the historical control group account for routine care. Potential control group patients were recruited at the start date of study implementation (January 2019) and, to attain the planned sample size, another cohort of patients was contacted half a year later (June 2019).

Potential patient participants are identified via a database search for all splenectomized patients within the predefined group-specific time periods since splenectomy by assistants of the AOK-Baden-Württemberg. Patients who meet criteria receive recruitment letters from the health insurance. Those who are interested in study participation receive detailed information on the procedure, the aims and the legal conditions of the study from the University Medical Centre Freiburg. Participants are asked to provide written informed consent and contact information if they agree to take part. Participants who participate in another clinical intervention trial at the same time are excluded from data analysis.

To identify potential physician participants, participating patients are asked to provide contact information on their general practitioner or other physician who mainly cares for their asplenia and sign an agreement releasing the practitioner form medical confidentially obligation. Physicians whose patients consent to having their physicians included in the study are recruited by letters with information concerning the study. No exclusion criteria for physicians are applied.

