**Procedure**

The chosen outcomes for patients are measured prior to the intervention (baseline measurement, t0), directly after the intervention (t1) and after a 6-month follow-up period (t2).

At t0, patients in the intervention group are sent paper-pencil pseudonymized questionnaires on baseline proximal and distal secondary outcomes and socio-demographic information. Upon receipt of the filled questionnaires, telephone appointments are arranged with patients for a study physician interview by study nurses. During telephone calls, a vaccination history, use and availability of stand-by antibiotics and the medical alert card are taken to gather baseline data on the primary outcome, the PrePSS-score, along with some other medical information relating to the patients’ asplenia (e.g. indication for splenectomy, splenectomy date and previous episodes of infection or PSS requiring hospitalization)

After t0-data collection, the patient-directed telephone-intervention is implemented. The intervention of the corresponding physician is conducted at about the same time; however, the order is determined by the arrangement of the telephone appointments and not standardized. Secondary physician outcomes are gathered after the physician-directed intervention. Historical control group patients and their physicians go through the same procedure and patients receive t0-questionnaires identical to intervention group patients, but only intervention participants continue measurement after the telephone intervention.

Following each patient telephone call, intervention patients complete post-intervention questionnaires on the proximal secondary outcomes similar to baseline items and evaluate the telephone-intervention (t1).

To test for six-month sustainability of the effects of the intervention they receive follow-up questionnaires on distal secondary outcomes identical to baseline measurement (t2). After return of the follow-up questionnaires, intervention patients are contacted by study physicians via telephone again to inquire the same set of data on the primary outcome and (changes in) medical data, such as the incidence of infections and PSS, gathered at t0.

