To ensure a valid data basis, patients’ self-report data on the primary outcome variable and on the medical information are confirmed with the corresponding physician both at t0 and (in the intervention group) at t2. In case physicians are interviewed prior to their patients, patients are made aware of any discrepancies between their information and information their physicians provided when required.

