**Data analysis**

Demographic characteristics of the study population and effect sizes in the intervention group will be reported descriptively. The main analysis tests the hypothesis that the PrePSS-score at follow-up is higher (better adherence to infection-risk reducing preventive measures) in the intervention group than in the control group. Due to the non-randomized design a propensity score adjustment is performed to reduce potential bias that may be caused by differences on covariates in the two groups (36). We will apply general linear models with propensity score as a covariate. The same method will be used for the analysis of secondary outcomes. Assuming missing data in the questionnaires, multiple imputation will be considered for corresponding analyses. Additional analyses will be conducted with structural equation modeling technique to test a priori specified mediation models of intervention effects.

A cost-effectiveness analysis of the intervention will be conducted by analyzing the change-from-baseline scores of the primary and the secondary outcomes in relation to the costs of the intervention. To reveal the economic efficiency of the intervention, routine data will be used to determine standard treatment and follow-up costs associated with infections requiring hospitalization and with PSS in asplenic patients to contrast them to the intervention costs.

In the qualitative analyses, the audio files of the interviews will be transcribed by an external service provider and the transcripts will be analyzed using a qualitative content analysis.

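### The cost-effectiveness analysis uses change from baseline, which only the intervention group has, so its effect is not incremental to usual care; the size and sign of the resulting error are unknown

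*Protocol*

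**What the plan says.** The Protocol's Data analysis section describes two economic elements. The first is the cost-effectiveness analysis, to be done by "analyzing the change-from-baseline scores of the primary and the secondary outcomes in relation to the costs of the intervention". No comparator is named. The second uses routine data to set the costs of hospitalised infections and post-splenectomy sepsis against the cost of the intervention.

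The measurement schedule is in Procedure. Outcomes are taken before the intervention (t0), "directly after the intervention (t1) and after a 6-month follow-up period (t2"). Control patients go through the same t0 steps, "but only intervention participants continue measurement after the telephone intervention". The section on the short version for the control group agrees: "Data collection relevant for the study has already been completed in this group at the time of intervention implementation". So does the check of self-report against the physician: data on the primary outcome "are confirmed with the corresponding physician both at t0 and (in the intervention group) at t2".

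Participants and recruitment defines the groups by time since surgery. "Potential intervention patients are recruited about 6-8 weeks after splenectomy", with four months as the upper limit for allocation to that group. "The historical control group consists of patients who are splenectomized since more than six months (at most 18 months"). The same section gives the purpose of the single control measurement: "pre-interventional baseline-data on primary and secondary outcomes in the historical control group account for routine care".

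The main analysis, also in Data analysis, compares the PrePSS-score of the intervention group at follow-up with the control group, with a propensity score as covariate. Secondary outcomes are to be analysed in the same way.

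**The concern.** A change score needs two measurements, and the control group has one. The effect entering the cost-effectiveness analysis is therefore a before-and-after difference in a single group. It contains whatever the intervention adds, plus whatever would have happened under usual care over the same months.

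The Protocol's own question is whether the intervention is superior to usual care, and it recruits a control group to answer that. The sentence on cost-effectiveness does not use that contrast. An insurer deciding whether to fund the programme needs the extra benefit for the extra cost. The planned figure does not estimate that, and the Protocol's expectation of lower insurer costs makes the economic result one that readers will use.

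**Working it through.** **Step 1: which group has which measurement** (Protocol, Procedure and the section on the control group's short version)

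| | t0 | After the intervention (t1, t2) | Change from baseline |
|---|---|---|---|
| Intervention | yes | yes | can be computed |
| Historical control | yes | no | cannot be computed |

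The structural point follows from this table alone.

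**Step 2: a plan figure to reproduce.** The cost-effectiveness analysis states none. The Protocol's sample size for the between-group comparison (100 per group; effect size 0.40, 80% power, two-sided 5%) does reproduce: 99 by the normal approximation, 99.1 before rounding up by the t-test. Nothing below depends on it.

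**Step 3: algebra.** Let B be the intervention mean at t0, F the intervention mean at t2, C the control mean standing for usual care (after adjustment), and K the incremental cost per patient.

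- Planned effect: F − B
- Incremental effect: F − C
- Difference: (F − B) − (F − C) = C − B
- Factor by which the effect is overstated: (F − B)/(F − C)
- Cost per point as planned: K/(F − B); incremental: K/(F − C)

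If f = (C − B)/(F − B) is the share of the rise that usual care would also bring, the factor equals 1/(1 − f). This gives 1.33 at f = 0.25, 2 at f = 0.5 and 4 at f = 0.75. The Protocol does not give f.

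**Step 4: illustration.** The Protocol gives no expected PrePSS means and no costs. The means below are assumptions on the 0–10 score.

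| B | C | F | F − B | F − C | Factor |
|---|---|---|---|---|---|
| 3 | 3 | 6 | 3 | 3 | 1.0 |
| 3 | 4 | 6 | 3 | 2 | 1.5 |
| 2 | 4 | 6 | 4 | 2 | 2.0 |
| 2 | 5 | 6 | 4 | 1 | 4.0 |
| 4 | 3 | 6 | 2 | 3 | 0.67 |

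Over a grid of B = 2 to 4, C = 3 to 5 and F = 5 to 7, restricted to B ≤ C < F, the factor runs from 1.0 to 4.0. In the second row the reported cost per point is (K/3)/(K/2) = 2/3 of the incremental one, so one third too low. The last row lies outside that restriction and shows the reverse: if C is below B, the planned analysis understates the benefit.

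**Step 5: what the Protocol says about direction.** Intervention patients are recruited early after surgery, and the score counts vaccinations, a stand-by prescription and an alert card, all of which routine care may still supply later. That makes C > B plausible. Background reports that only 6% of patients in regular care had completed the vaccination schedule and 47% had stand-by prescriptions. These figures are not broken down by time since splenectomy, so they neither establish nor exclude a rise under usual care.

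**The case against.** The best defence is that the weakness sits in one sentence about an ancillary analysis. The main analysis is between groups and propensity-adjusted, secondary outcomes follow the same method, and the infection-cost element uses no change scores. The sentence also does not promise an incremental ratio. All of this is true, and the primary and secondary outcome conclusions are untouched. But the infection-cost element supplies no usual-care comparator for the score-based effect. Nor is this a detail merely left to an analysis plan: the Protocol itself fixes the effect measure.

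The defence is also right about several stronger readings that a reader might infer.

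- *The intervention will look cheaper per unit of benefit than it is.* This needs C > B, which the Protocol does not establish.
- *Vaccination courses are still running at t0.* The Protocol does not say so. How a part-complete course scores is set out in a supplement that is not at hand.
- *t0 falls between 6–8 weeks and four months after splenectomy.* The first figure is the time of recruitment and the second the limit for allocation. Consent, return of the questionnaire and a telephone appointment come before the t0 interview, and no t0 window is stated.
- *A contrast at matched time since splenectomy is already estimated in the main analysis.* The main analysis states no such alignment.

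**Conclusion.** The point holds as a structural flaw. Following the Protocol as written gives a single-group before-and-after effect, which is not incremental to the usual-care comparator that the Protocol sets for itself. This rests only on the measurement schedule.

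The error equals C − B. Its size and sign cannot be derived from the Protocol: it is zero if C = B, an overstatement of benefit per cost if C > B, and an understatement if C < B. Overstatement is plausible given early recruitment, but it is not shown. The range of 1.0 to 4.0 rests wholly on assumed means with C at or above B and is no estimate for this trial. Reading C − B as the gain under usual care further assumes that the adjusted control group is a fair stand-in for the intervention patients. The consequence is confined to the cost-effectiveness result, and the change should be made before that result is reported.

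**What to change.** In Data analysis, replace the change-from-baseline effect with the propensity-adjusted difference between the intervention group at t2 and the control group. Do this for the primary outcome and for those secondary outcomes measured in both groups. Procedure schedules the proximal scales at t1 rather than t2, so the text should name the time point used for them. Relate the difference to the incremental cost against usual care and report an interval. Keep the within-group change as description only.

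The edit is short and needs no new outcome measurements, because this contrast is already the planned main analysis. It has three costs.

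- The contrast remains non-randomised.
- Time since splenectomy is only roughly comparable. If t0 is assumed to fall at about 2–4 months, t2 falls at about 8–10 months (adding 6), against more than 6 and up to 18 months in controls. This should be stated as a limitation. Closer alignment would need restriction or further modelling.
- The ratio may become less favourable to the intervention.

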# Discussion

Poor implementation of the prevention recommendations for patients without a functioning spleen has been demonstrated in several studies. Better adherence to preventive measures is urgently needed (2, 11). However, conclusive and effective new strategies to improve care beyond the passive provision of information have not yet been described for asplenic patients.

Strengths of the current study are the development and evaluation of a theory-based dual intervention, i.e. focusing on patients and their physicians. By educating and training patients, the intervention contributes to the empowerment of the patients. Quantitative data will allow us to evaluate the effect of the intervention on prevention measures such as vaccinations, prophylactic and stand-by antibiotic use and patient-related outcomes*.* Qualitative interviews will enable us to understand e.g. barriers in preventive behaviour. Furthermore, the new intervention can be improved on the basis of feedback from asplenic patients and their physicians. Following this evaluative process, the intervention-manual will be made publicly available on the German website ‘asplenie.net’ to enable future implementation in practice.

The study has some limitations, which are mainly based on our sampling strategy. First, our sample contains a self-selected group of patients from the cooperating health insurance (AOK Baden-Württemberg). Secondly, it is not a randomized controlled trial, however, due to above outlined ethical reasons randomization is not justifiable. In order to reduce a potential bias that may be caused by differences in covariates in the intervention vs. historical control group, propensity score matching will be applied. Third, the primary outcome, the PrePSS-score was developed via expert-ratings, however, weighting of the four included items may still need further refinement and research.

All in all, we believe that the experience gained with this type of intervention will also be very valuable for prevention strategies in patients with other diseases. The intervention could be considered - after demonstrated effectiveness - in the context of other poorly implemented primary prevention measures or standard vaccinations, e.g. influenza and pneumococcal vaccination in patients over the age of 60 years.

# List of abbreviations

GAD-2: Generalized Anxiety Disorder Scale; HAPA: Health Action Process Approach; heiQ: Health Education Impact Questionnaire; HLQ: Health Literacy Questionnaire; MHB-39: Questionnaire of Multiple Health Behavior; OPSI: Overwhelming post-splenectomy infection; PHQ-2: Patient-Health-Questionnaire; PHQ-4: Patient Health Questionnaire for Depression and Anxiety; PICS: Perceived Involvement in Care Scales; PrePSS-score: Preventing PSS-score; PSS: Post-splenectomy sepsis; SEVERA: Section of Health Care Research and Rehabilitation Research; SF-12: 12-item Short-Form-Health-Survey

